#### Blood biomarkers

Venous blood samples will be obtained after a 10 to 12-hour overnight fast by venepuncture (EDTA-containing tubes) and will be centrifuged within two hours of sampling. Plasma will be removed and erythrocytes will be washed with saline. Aliquots of plasma and erythrocytes will be stored at −80°C until analysis. Relative proportions of individual fatty acids in erythrocyte phospholipids will be assessed using a method adapted from previously established methods [43-45] and described in detail by Milte *et al*. [46]. In this process fatty acids will be extracted and transmethylated and the methyl esters will be separated and quantified using a Shimadzu 2010 gas chromatograph (Shimadzu, Milan, Italy). Fatty acid methyl esters will be identified by comparing retention times to those of authentic lipid standards (GLC-463, Nu-Chek Prep Inc. Elysian, MN, USA). Inflammatory biomarkers including tumor necrosis factor (TNF-α), interleukin-1 beta (IL-1β) and interleukin-6 (IL-6) and the anti-inflammatory biomarker interleukin-10 (IL-10) will be analyzed in duplicate using multiplex Luminex analyzer (Luminex B.V., Oosterhout, The Netherlands) assays. Intra- and inter-assay coefficients of variation (CV) are 5 to 14% and 4 to 18%, respectively. High sensitivity C-reactive protein will be measured using an automated spectrophotometric analyzer (Konelab, Model 20xTi; Thermo Electron, Waltham, MA, USA); the CV for this determination is 2.3%.

#### Pulmonary function

Lung function tests will follow standardized American Thoracic Society/ European Respiratory Society taskforce guidelines [47] to determine forced expiratory volume in 1 second (FEV_1_), forced vital capacity (FVC), inspiratory capacity (IC) and vital capacity (VC), which enables the diagnosis and severity classification of COPD. Small airways function will be assessed using two methods: forced expiratory flow will be measured at various time points (FEF_25-75_, FEF_25_, FEF_50_, FEF_75_) [47] and impulse oscillometry will be used to determine respiratory impedance through the application of small pressure oscillations at the mouth during normal breathing [48]. Single-breath determination of carbon monoxide (CO) uptake will be used to determine the gas transfer efficiency of the lung tissue as the diffusing capacity of carbon monoxide (*D*L, CO) [49], which is reduced in the presence of emphysema and some other conditions. Lung volumes will be determined using body plethysmography [50].

#### Dyspnea

The sensation of dyspnea is currently considered to have three domains (sensory quality, intensity and unpleasantness). The Dyspnoea-12 questionnaire will be used to assess the sensory quality of breathlessness. Visual analogue scales (10 cm horizontal line anchored on the left as unaffected) will be used to quantify unpleasantness (not unpleasant to worst unpleasantness imaginable) and intensity (no breathlessness to the worst possible breathlessness) of dyspnea. Assessments of dyspnea will be conducted at rest (average sensation over the past two weeks) and immediately after the six-minute walk test (breathlessness induced by exercise). The mMRC score will be used to assess dyspnea related functional impairment, with a scoring system of 0 to 4 (where 4 represents severe breathlessness related impairment). The mMRC scale is widely used in people with COPD and is a reliable (intraclass correlation = 0.82) [51] tool with acceptable concurrent validity (*r* = 0.70) [52].

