### Feasibility outcomes and criteria

Within the four domains of feasibility (process, resources, management and scientific) there are specified outcomes in the process and resource domains that will be assessed throughout the study against feasibility criteria (see Table 2).

**Table 2 T2:** Feasibility outcomes and key feasibility criteria

**Outcome**	**Outcome measure**	**Key feasibility criteria**
*Process*		
Recruitment rate	Number of participants recruited per week.	Recruit 40 participants in 52 weeks.
Retention rate	Number of participants completing the intervention.	Complete the intervention in 80% of all recruited participants.
Supplement adherence rate	Symptom diary.	
	Change in RBC total LCn-3PUFA content.	≥2% change in total RBC LCn-3PUFA.
	Capsule count at study completion.	≥80% of capsules consumed.
Refusal rate	Number of identified volunteers who decline to participate/randomize.	
Time lost to exacerbation	Symptom diary.	
*Scientific*		
Supplement safety	Reported symptoms from supplement.	
Estimate effect size	Listed scientific outcomes.	A positive moderate effect size (≥0.2) in at least CRP, dyspnea and FEF_25-75_.
Estimate variance	Standard deviations of listed outcomes.	

CRP, C-reactive protein; FEF_25-75_, forced expiratory flow between 25 and 75% of forced vital capacity; LCn-3PUFA, long chain omega-3 polyunsaturated fatty acid; RBC, red blood cell.

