#### Functional exercise capacity

The six-minute walk test will be used to determine change in functional exercise capacity (six-minute walk distance). Participants walk on a hard flat surface as far as they can in six minutes (one lap up and back = 40m), stopping for breaks if required. The test will be conducted twice with the maximum walk distance used for analysis. The six-minute walk test is a reliable (CV = 8%, intra-class correlation coefficient = 0.93) measure when conducted under standardized conditions [53,54] and is commonly used as an indicator of functional exercise capacity in the COPD population [55-57] as well as other chronic diseases such as cardiovascular disease [58].

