#### Well-being

The Hospital Anxiety and Depression Scale (HADS), a widely used reliable validated tool [59] will be used to assess symptoms of depression and anxiety [60]. The HADS has been used previously in the COPD population with good reliability (Cronbach’s α = 0.86 (part A) and 0.87 (part B)) [61]. The chronic respiratory questionnaire (CRQ) is a self-administered respiratory specific quality of life questionnaire with good reliability [62] and validity [63]. The questionnaire assesses four domains including dyspnea, fatigue, emotional function and mastery [62].

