### Data analysis

SPSS version 17 for WINDOWS [International Business Machines Corporation (IBM), New York, USA] will be used for analyses. Data will be cleaned, checking for errors or missing values. Continuous data will be checked for normality of distribution and non-normally distributed data will be transformed where possible. Scatter plots will be used to determine nature/shape of relationships before applying linear regression.

The primary focus of this study is feasibility, which will be analyzed using descriptive statistics and frequency tables. The key feasibility outcomes are:

1. Recruit 40 participants in 52 weeks;

2. Complete the intervention in 75% of all recruited participants;

3. ≥2% change in total erythrocyte LCn-3PUFA and ≥80% of capsules consumed (estimated from remaining capsules);

4. A positive moderate effect size (≥0.2) in at least three scientific outcome measures (between active and placebo groups).

Analysis of variance (ANOVA) with repeated measures will be used to estimate the effect size of LCn-3PUFA versus placebo supplementation on the scientific outcome measures (six-minute walk, pulmonary function tests, questionnaire scores, blood biomarkers of inflammation and symptoms (for example, high sensitivity C-reactive protein, dyspnea and impulse oscillometry)). Progressive Bonferroni corrections will be used to correct for the effects of multiple outcomes. Comorbid status and severity of exacerbations will be assessed as potential confounders using multiple regression analysis.

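### The effect-size criterion in Table 2 includes dyspnea without saying which of five to eight dyspnea scores counts, and two other sections state a different rule

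*Protocol article*

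**What the plan says.** Table 2 (Feasibility outcomes and criteria) sets this key criterion for the effect-size estimate: "A positive moderate effect size (≥0.2) in at least CRP, dyspnea and FEF_25-75". It names no dyspnea instrument, domain or condition.

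The Dyspnea section treats dyspnea as having three domains and measures each separately. For the first, "The Dyspnoea-12 questionnaire will be used to assess the sensory quality of breathlessness". For the other two, visual analogue scales (VAS) "will be used to quantify unpleasantness (not unpleasant to worst unpleasantness imaginable) and intensity (no breathlessness to the worst possible breathlessness) of dyspnea". On timing, "Assessments of dyspnea will be conducted at rest (average sensation over the past two weeks) and immediately after the six-minute walk test (breathlessness induced by" […]. The section adds mMRC as a measure of functional impairment due to dyspnea. Under Well-being, the CRQ contributes another candidate: "The questionnaire assesses four domains including dyspnea, fatigue, emotional function and mastery".

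Data analysis words the criterion differently: "A positive moderate effect size (≥0.2) in at least three scientific outcome measures (between active and placebo groups"). The Abstract likewise asks for a moderate effect in at least three efficacy measures. Neither makes dyspnea obligatory.

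**The concern.** A numeric threshold gives a determinate answer only if the quantity compared with it is fixed. Table 2 does that for two legs. It takes CRP from five blood markers, and FEF25-75 from several flow measures and impulse oscillometry. The third leg is left as a construct with several scores under it. Those scores cover different domains and two conditions, so they can fall on different sides of 0.2 in the same data.

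If the score is chosen after the results are known, the dyspnea leg is easier to pass than a threshold of 0.2 suggests. If a score that happens to fall short is chosen, the leg fails although others passed. Neither outcome tells the reader whether the stated criterion was met.

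**Working it through.** **Inputs from the protocol article**
- Sample Size: 40 enrolled, 25% dropout, 30 completers. Check: 30 / (1 − 0.25) = 40, which reproduces the stated target. Equal arms are assumed, so n = 15 per arm.
- Table 2: threshold 0.2.
- Not given: the effect-size metric and the correlation between dyspnea scores. I assume a standardised mean difference d, and a common correlation r between scores of 0.3 to 0.7.

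**Number of candidate scores**
- Narrow count: Dyspnoea-12 at rest (1) + two VAS × two conditions (4) = 5.
- Wide count: Dyspnoea-12 × two conditions (2) + two VAS × two conditions (4) + mMRC (1) + CRQ dyspnea domain (1) = 8.

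**One score named beforehand, no true effect**
- SE(d) ≈ √(2/n) = √(2/15) = 0.365.
- z = 0.2 / 0.365 = 0.548.
- P(d ≥ 0.2) = 1 − Φ(0.548) = 0.292, or 29%.

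**Best of k scores, no true effect**

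For equally correlated normal scores that share a common factor X ~ N(0, 1):

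P(at least one ≥ 0.2) = 1 − E{Φ[(0.548 − √r·X) / √(1 − r)]^k}

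| k | r = 0.3 | r = 0.5 | r = 0.7 |
|---|---|---|---|
| 5 | 70% | 62% | 54% |
| 8 | 80% | 71% | 60% |

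Even at r = 0.9, eight scores give 46%.

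**Scores that disagree**

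The share of null trials in which some scores pass and others fail is 44% (r = 0.7) to 68% (r = 0.3) for five scores, and 53% to 80% for eight.

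**Whole effect-size criterion, all three legs required and assumed independent**
- CRP and FEF25-75 both pass: 0.292² = 0.085.
- With one named dyspnea score: 0.085 × 0.292 = 0.025, or 2.5%.
- Best of five: 0.085 × 0.54 = 0.046 to 0.085 × 0.70 = 0.060.
- Best of eight: 0.085 × 0.60 = 0.051 to 0.085 × 0.80 = 0.068.

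So the false-pass chance of the whole criterion goes from about 2.5% to about 5% to 7%.

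**The two rules side by side**

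Table 2 names three outcomes. Data analysis and the Abstract accept any three. Under the looser rule, three dyspnea scores could satisfy the criterion between them, because nothing says that they count once.

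**The case against.** The best case for the plan is its purpose. This is a feasibility study, and Scientific outcome measures says that many outcomes are collected so that suitable ones can be chosen for a later trial. Having several dyspnea scores is deliberate, and nothing in the article permits picking the best one. That stands as a defence of measuring them all. It does not rescue a threshold that the article itself sets on an undefined quantity. Nor is this detail that can be left to an analysis plan, since the article states the criterion, the threshold and the outcomes.

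A second objection concerns the count. Eight is the upper limit: CRQ sits under Well-being, mMRC is described as functional impairment and is also the minimization factor, and a post-walk Dyspnoea-12 is inferred from a general sentence. This is fair, which is why the range starts at five.

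Third, the 54% to 80% refers to one leg. A reader might infer that the choice of score decides the trial's overall verdict that often. It does not. Under Table 2 the choice matters only when CRP and FEF25-75 both pass, about 8.5% of null trials if independent. Recruitment, retention and adherence are separate criteria.

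A reader might also infer that post-walk dyspnea is mismatched with the analysed distance, because "The test will be conducted twice with the maximum walk distance used for analysis" and the test order puts questionnaires after the first walk. The article does not say which walk supplies the post-exercise rating, does not rule out a rating after the second, and plans no analysis that pairs rating with distance. That a self-paced walk hides benefit is likewise not shown: resting dyspnea and distance are both measured.

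**Conclusion.** The point holds in a limited form. The dyspnea leg of Table 2 has no determinate result, because five to eight scores qualify. With no true effect, choosing among them afterwards raises the chance of passing that leg from 29% to 54% to 80%, roughly a doubling or more. For the effect-size criterion as a whole, under Table 2's rule, the rise is from about 2.5% to about 5% to 7%, which is modest in absolute terms.

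These figures assume 15 per arm, equal arms, a standardised mean difference, correlations of 0.3 to 0.7 between dyspnea scores and, for the whole criterion, independence of the three legs. The article gives none of these except the 30 completers. The direction does not depend on them: the chance still rises at a correlation of 0.9.

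The conflict between Table 2 and the any-three rule in the Abstract and Data analysis is part of the same problem, since naming a score in Table 2 alone would not settle which outcomes count. The documents do not support any conclusion about which walk the post-exercise ratings belong to.

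**What to change.** Before unblinding:

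1. Reconcile Table 2 with the Abstract and Data analysis so that one effect-size rule applies throughout.
2. In that rule, replace the word dyspnea with one named score and condition, for example the resting Dyspnoea-12 total.
3. Report all other dyspnea scores, with their effect sizes and variances, without counting them towards the criterion.

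This is a change of wording only. All outcomes are still collected for choosing endpoints of a later trial, and no visit, test or participant is added. The downside is that the criterion becomes harder to meet, because a single score has to carry the dyspnea leg.

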#### Functional exercise capacity

The six-minute walk test will be used to determine change in functional exercise capacity (six-minute walk distance). Participants walk on a hard flat surface as far as they can in six minutes (one lap up and back = 40m), stopping for breaks if required. The test will be conducted twice with the maximum walk distance used for analysis. The six-minute walk test is a reliable (CV = 8%, intra-class correlation coefficient = 0.93) measure when conducted under standardized conditions [53,54] and is commonly used as an indicator of functional exercise capacity in the COPD population [55-57] as well as other chronic diseases such as cardiovascular disease [58].

#### Well-being

The Hospital Anxiety and Depression Scale (HADS), a widely used reliable validated tool [59] will be used to assess symptoms of depression and anxiety [60]. The HADS has been used previously in the COPD population with good reliability (Cronbach’s α = 0.86 (part A) and 0.87 (part B)) [61]. The chronic respiratory questionnaire (CRQ) is a self-administered respiratory specific quality of life questionnaire with good reliability [62] and validity [63]. The questionnaire assesses four domains including dyspnea, fatigue, emotional function and mastery [62].

### Data analysis

SPSS version 17 for WINDOWS [International Business Machines Corporation (IBM), New York, USA] will be used for analyses. Data will be cleaned, checking for errors or missing values. Continuous data will be checked for normality of distribution and non-normally distributed data will be transformed where possible. Scatter plots will be used to determine nature/shape of relationships before applying linear regression.

The primary focus of this study is feasibility, which will be analyzed using descriptive statistics and frequency tables. The key feasibility outcomes are:

1. Recruit 40 participants in 52 weeks;

2. Complete the intervention in 75% of all recruited participants;

3. ≥2% change in total erythrocyte LCn-3PUFA and ≥80% of capsules consumed (estimated from remaining capsules);

4. A positive moderate effect size (≥0.2) in at least three scientific outcome measures (between active and placebo groups).

Analysis of variance (ANOVA) with repeated measures will be used to estimate the effect size of LCn-3PUFA versus placebo supplementation on the scientific outcome measures (six-minute walk, pulmonary function tests, questionnaire scores, blood biomarkers of inflammation and symptoms (for example, high sensitivity C-reactive protein, dyspnea and impulse oscillometry)). Progressive Bonferroni corrections will be used to correct for the effects of multiple outcomes. Comorbid status and severity of exacerbations will be assessed as potential confounders using multiple regression analysis.

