**Methods/Design:**

A 16-week parallel, double-blind, randomized, placebo-controlled dietary supplementation trial will be evaluated. Forty participants meeting spirometric and clinical criteria for COPD will be recruited from metropolitan Adelaide, South Australia. Participants will be randomized by minimization, based on a score derived from the modified Medical Research Council Scale for breathlessness, to receive 6 g/day of fish oil (approximately 3.6 g/day of LCn-3PUFA), or placebo (6 g/day of corn oil) capsules. Feasibility outcomes (recruitment, retention, supplement adherence, and time lost to exacerbation) and scientific outcomes (effect size and estimates of variance for inflammatory biomarkers, incorporation of LCn-3PUFA into erythrocytes, small airways function, dyspnea and functional exercise capacity) will be assessed pre- and post-intervention. Key feasibility criteria include recruitment of 40 participants in 52 weeks, 75% participant retention rate, 2% increase in the proportion of long-chain omega-3 fatty acids in erythrocytes, and a positive moderate effect size in at least three efficacy measures.

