### Sample Size

As this is a feasibility study designed to determine pragmatic aspects of methodology, formal sample size calculations are not appropriate [26,29]. The target sample size for the feasibility study is 40 participants. The target sample is to allow sufficient precision to enable sample size calculations for subsequent studies. Browne [30] suggests that a minimum of 30 participants is required to achieve sufficient precision, a recommendation supported by Lancaster *et al*. [31]. The target sample of 40 enrolled participants will allow completion of 30 subjects, allowing for a 25% participant dropout rate. A key feasibility criterion is the ability to recruit a target sample of 40 participants within 52 weeks.

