### Dietary intervention

Participants will be required to take six 1 g capsules orally per day for 16 weeks. The fish oil group will consume capsules containing EPAX 6000 TG/N omega-3 concentrate (EPAX, Oslo, Norway). Each capsule contains 600 mg of omega-3 fatty acids, which is specified to contain 200 mg of DHA and 300 mg of EPA. It should be noted that while the recommended upper limit of LCn-3PUFA is 3 g/day [34], a number of studies have used higher doses (3.4 g/day to 6.6 g/day) without any reported side effects [35,36]. The placebo group will receive capsules that are identical in appearance containing corn oil (predominantly comprised of linoleic, oleic and palmitic acids) (EPAX, Oslo, Norway). All capsules are flavored to mask the taste and odor. Participants will continue their usual medical treatment throughout the supplementation period. Self-reported medication and supplement use will be collected pre- and post-intervention.

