#### Process outcome measures

A number of process outcomes will be assessed throughout the study including participant recruitment and retention, supplement adherence, time lost to exacerbation and participant experiences and perspectives about participating in the study. Participant recruitment and retention will be assessed descriptively by recruitment and refusal rates, while retention will be determined by the number of enrolled participants who complete the study protocol.

Supplement adherence will be assessed in three ways. Firstly, by determining changes from baseline to post-intervention in the LCn-3PUFA content of erythrocytes, as the LCn-3PUFAs are incorporated into erythrocyte membranes in a dose-dependent and time-dependent manner [41]. Secondly, a symptom diary will be used to document self-reported supplementation consumption including whether the capsules were consumed each day, how many capsules were consumed and whether any side effects were experienced such as eructation or heartburn. Thirdly, participants will be asked to return all unused capsules at the completion of the study and the remaining capsules will be counted.

The time lost to exacerbation (change in usual symptoms potentially leading to a change in medication, change in usual activities or unscheduled visit to a doctor) will be determined using a symptom diary in the format of one month per page. The diary enables the assessment of exacerbation frequency and severity during the supplementation period. The number of exacerbation days will be counted from the diary, while an exacerbation severity score will be calculated using methods adapted from those described by Effing *et al*. [42]. Data collected from the symptom diary will be used to determine the frequency of exacerbation, whether periods of exacerbation impact upon supplement consumption and whether periods of exacerbation have a confounding effect on supplementation or study outcomes. This information will be used to determine whether exacerbations during the supplementation period should be an exclusion criterion in a subsequent study.

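### Retention is judged on both arms pooled and no key criterion covers tolerability, so good placebo retention can mask poor fish oil retention

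*Protocol article*

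**What the plan says.** - **Retention, Data analysis, key outcome 2:** "Complete the intervention in 75% of all recruited participants". The Abstract gives the same level ("75% participant retention rate").
- **Retention, Table 2:** "Complete the intervention in 80% of all recruited participants". The threshold differs; the pooled denominator is the same.
- **Definition, Process outcome measures:** "retention will be determined by the number of enrolled participants who complete the study protocol". There is no split by arm.
- **Sample Size:** "The target sample of 40 enrolled participants will allow completion of 30 subjects, allowing for a 25% participant dropout rate".
- **Safety, Table 2:** the supplement safety row has the measure "Reported symptoms from supplement" and an empty criterion cell. The four key outcomes in Data analysis are recruitment, retention, adherence (erythrocyte change and capsules) and effect size.
- **Adherence, key outcome 3:** at least a 2% change in erythrocyte LCn-3PUFA and at least 80% of capsules taken. Neither the arm nor the denominator is given, and Process outcome measures has unused capsules returned and counted at the end of the study.
- **Tolerability in the protocol's own words:** Dietary intervention notes that "while the recommended upper limit of LCn-3PUFA is 3 g/day [34], a number of studies have used higher doses". The Abstract puts the trial's own intake at about 3.6 g/day. Process outcome measures names eructation and heartburn as possible side effects.

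**The concern.** The trial is meant to show, among other things, whether people with COPD can keep taking this supplement for 16 weeks. That question is about the fish oil arm. A pooled retention rule answers a different one: whether enough participants in total reach the end. If fish oil is poorly tolerated and placebo is not, the placebo arm can carry the pooled figure over the threshold.

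No other key outcome is a tolerability criterion. Symptoms are recorded, but no result on them is tied to a threshold. A larger trial planned on a passed retention criterion could then inherit dropout that depends on the arm, which biases a comparison of completers and cannot be cured by recruiting more people.

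**Working it through.** **Inputs.** 40 recruited and 25% dropout (Sample Size); thresholds of 75% (Abstract, Data analysis) and 80% (Table 2). Assumptions: 20 per arm, because the Randomization section gives no ratio (18 to 22 on fish oil is shown as a range), and the true dropout rates below, which are illustrations and not figures from the protocol.

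**Step 1: the plan's own figure.** 30 / (1 − 0.25) = 40. It reproduces.

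**Step 2: worst case that still passes.**
- At 75%: 0.75 × 40 = 30 completers, so 10 may stop. All on fish oil: 10/20 = 50% (10/22 = 45% to 10/18 = 56%).
- At 80%: 0.80 × 40 = 32 completers, so 8 may stop. All on fish oil: 8/20 = 40% (8/22 = 36% to 8/18 = 44%).
- The same threshold applied within the fish oil arm allows at most 5/20 stoppers at 75% and 4/20 at 80%.

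**Step 3: how often each rule passes.** Let X be dropouts on fish oil, Binomial(20, d_F), and Y dropouts on placebo, Binomial(20, d_P), independent.
- Pooled rule: P(X + Y ≤ 10) at 75%; P(X + Y ≤ 8) at 80%.
- With the fish oil condition added: P(X + Y ≤ 10 and X ≤ 5) at 75%; P(X + Y ≤ 8 and X ≤ 4) at 80%.

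| d_F / d_P (assumed) | 75%: pooled | 75%: with fish oil arm | 80%: pooled | 80%: with fish oil arm |
|---|---|---|---|---|
| 40% / 5% | 0.739 | 0.126 | 0.426 | 0.051 |
| 40% / 10% | 0.586 | 0.125 | 0.285 | 0.049 |
| 40% / 15% | 0.436 | 0.120 | 0.179 | 0.044 |
| 40% / 25% | 0.198 | 0.088 | 0.058 | 0.025 |
| 10% / 10% | 0.999 | 0.988 | 0.985 | 0.950 |
| 15% / 15% | 0.970 | 0.920 | 0.865 | 0.777 |
| 20% / 20% | 0.839 | 0.743 | 0.593 | 0.495 |
| 25% / 25% | 0.584 | 0.482 | 0.300 | 0.236 |

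The first four rows show what the added condition catches; the last four show what it costs.

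**Step 4: does key outcome 3 close the gap?** Take 10 fish oil stoppers who each took capsules for a fraction f of the 16 weeks, with everyone else taking all of them.
- Counted in completers only: no limit on stopping.
- Counted over all 40: (30 + 10f)/40 ≥ 0.80 gives f ≥ 0.20, or 3.2 weeks.
- Counted over the 20 on fish oil: (10 + 10f)/20 ≥ 0.80 gives f ≥ 0.60, or 9.6 weeks.

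On the strictest reading outcome 3 does bind, but half the fish oil arm can still stop early and pass it. The erythrocyte and effect-size criteria need a post-intervention measurement, so as written they mainly reflect completers.

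**The case against.** **The adherence criterion already covers tolerability.** Partly right. Capsule intake is a direct measure of whether people can take the product, and a rise in erythrocyte LCn-3PUFA makes sense as a target only on fish oil. A reader might infer that pooled retention is the only key figure able to register intolerance, or that the whole trial would be declared feasible with half the fish oil arm lost. The protocol supports neither: outcome 3 can register intolerance, and outcomes 3 and 4 are also listed as key. What stands is that outcome 3 is an incomplete guard (step 4).

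**The 50% figure depends on one of two thresholds.** Correct. At Table 2's 80% the ceiling is 40% and the pass probabilities are lower. Pooling remains at either level.

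**The illustration pairs high fish oil dropout with low placebo dropout.** Fair. The Background reports high dropout in COPD trials. With placebo dropout at 25%, the gap at the 75% threshold shrinks to 0.198 against 0.088.

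**Safety is collected.** It is, by symptom diary and exit interview, so it would be wrong to infer that tolerability goes unmeasured. The gap is the missing threshold, not missing data.

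**There is no mechanical go/no-go rule, and pooling suits the aim of 30 completers.** Feasibility is to be described and to guide later work, and investigators would see a lopsided split. Pooled retention is also coherent with the sample size reasoning. That makes this a choice to improve, not an error. But the article does print criteria and their denominator, so this is not merely detail left to a fuller document.

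**Conclusion.** The point holds in a limited form. The retention criterion as printed allows placebo completers to offset fish oil losses, up to 10/20 fish oil stoppers at 75% or 8/20 at 80%, assuming equal arms; both are worst cases. No key criterion is set for safety or tolerability, and key outcome 3 compensates only in part.

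The practical size depends on how different the arms are. At an assumed 40% dropout on fish oil and 5% to 10% on placebo, the pooled rule passes about four to six times as often as one that also looks at the fish oil arm at 75% (0.739/0.126 = 5.9; 0.586/0.125 = 4.7). The ratio falls to about 2 when placebo dropout is 25% (0.198/0.088 = 2.3). Nothing in the protocol says which of these is likely.

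This is a cheap improvement, between optional and advisable. It takes no view on the dose.

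**What to change.** 1. Reconcile the 75% in the Abstract and Data analysis with the 80% in Table 2.
2. Word key outcome 2 so that the chosen threshold is to be met overall and in the fish oil arm (with 20 in that arm, at least 15 completers at 75% or 16 at 80%). State that a miss in the fish oil arm alone means tolerability is reviewed before a larger trial is recommended. This softens a cut-off that is noisy with 20 people.
3. Next to the criterion, report by arm how many stop the capsules and how many stop because of side effects.

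**Cost.** One sentence in Data analysis and one row in Table 2. Completion, capsule use and side effects are already recorded, and the article gives the trial status as not yet recruiting. The real price is a lower chance of meeting the criterion outright when dropout is the same in both arms. At 75% it falls from 0.97 to 0.92 with 15% dropout, from 0.84 to 0.74 with 20%, and from 0.58 to 0.48 with the protocol's own planning figure of 25%.
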